### Participants

Patients with an ASA grade I–IV, age ≥ 70 years, and undergoing noncardiac surgery will be chosen from February 2022 to December 2023. The preoperative assessment will make use of the mFI and MMSE. Patients in the nonfrailty group will have a mFI < 0.21, and those in the frailty group will have a mFI ≥ 0.21. Enrollment will end once the projected sample size of patients in both groups has been reached.

### Sample size calculation

The main outcome will be the incidence of POD. Based on literature review and early study results, the estimated incidence of frailty in surgical patients was 23.0%, while the incidence of POD in the frailty and nonfrailty groups was 35.7% and21.7%. PASS 15.0 software was used to determine the sample size for the independent sample rate comparison of the two groups. The ratio of samples between the experimental and control groups was 0.303, and the two-sided test. Test level (α), and inspection effectiveness (1-β) were set at 0.05 and 0.80, respectively. This calculation yielded a sample size of 112 patients in the frailty group and 370 patients in the nonfrailty group. Considering 10% dropout rate, a total of 536 study volunteers will be required, consisting of 411 patients in the nonfailty group and 125 patients in the failty group.

### Eligibility criteria

Inclusion and exclusion criteria are listed in Table 1.

**Table 1 pone.0295500.t001:** Inclusion and exclusion criteria.

Eligibility criteria
Inclusion criteria Age ≥ 70 years; ASA I—IV level; Patients with a signed the informed consent form for the clinical study; Patients scheduled to undergo noncardiac surgery. Exclusion criteria Refuse to participate; Hospital stay <3 days; Emergency surgery; Patients can only be included once, regardless of whether the cause of the second operation is related to the first cause; Speech impairment or severe hearing or vision impairment that prevents communication; Central nervous system diseases (dementia, depression); Severe renal insufficiency (requiring dialysis); Severe abnormal liver function (Child-Pugh score ≥ 10); Participation in other relevant clinical studies within 3 months; MMSE examination confirmed the existence of cognitive dysfunction: illiteracy ≤ 17 points, primary school level ≤ 20 points, secondary school level (including technical secondary school) ≤ 22 points, university level (including junior college) ≤ 23 points.

### Shedding criteria

Study participants who refuse to provide informed consent or withdraw from the study.

### Study implementation

All members of the research team will receive systematic training to master and use the MMSE, aCCI, mFI, BI, 3D-CAM, and CAM-ICU before the study and may only participate after passing the examination.

**Preoperative frailty assessment:** The mFI is a National Surgical Quality Improvement Gauge (NSQIP)-based 11-factor index that has been proven to adequately reflect frailty and predict mortality and morbidity [32]. The mFI is calculated by dividing the number of factors present for a patient by the number of available factors for which there are no missing data [33]. An mFI score of 0 is classified as healthy, 0–0.21 is classified as a prefrail, and ≥ 0.21 is classified as a prefrail. The index includes 11 items: nonindependent function or activity status; history of diabetes; history of chronic obstructive pulmonary disease (COPD) or pneumonia; history of congestive heart failure; history of myocardial infarction; angina pectoris, percutaneous coronary intervention (PCI), cardiac surgery; hypertension requiring medication; peripheral vascular disease or static pain; sensory disturbance; transient ischaemic attack (TIA) attack or cerebrovascular accident without sequelae; cerebrovascular accident with sequelae [34]. In this study, patients with moderate and severe dysfunction with a BI ≤ 60 are considered to be positive for item 1. The advantage is that it has been employed and is frequently used in the risk classification of various surgical operations in the NSQIP database of the United States.The majority of evaluation indexes are comorbidities, poor nutrition, metabolism, and other physical function indexes, which is a drawback.**Assessment of activities of daily living:** The patients will be assessed preoperatively by the BI evaluation form; 0–40 is classified as severe dysfunction, 41–60 is classified as moderate dysfunction, 61–99 is classified as mild dysfunction, and 100 is classified as self-care.**Diagnosis of POD:** The 3D-CAM will be used to evaluate POD twice a day (8:00–10:00 and 18:00–20:00) on the the 1^st^ to 7^th^ postoperative days. The 3D-CAM provides a brief assessment (3 orientation items, 4 attention items, 3 symptom probes, and 10 observational items) that facilitates rating of the 4 core CAM features and has a sensitivity of 95% and specificity of 94% when compared with a clinical reference standard rating in a prospective validation study in hospitalized patients [35].

### Primary outcome

The primary outcome will be the incidence of POD.

### Secondary outcomes

The incidence of 30-day readmission, one-year all-cause mortality, postoperative complications (such as pulmonary infection, urinary tract infection, cardiovascular and cerebrovascular accidents, abnormal liver function, postoperative bleeding, incision infection, lower extremity deep venous thrombosis, electrolyte disorder, and hypoproteinemia), and postoperative complications (such as infection of the incision, infection of the incision site, and postoperative bleeding) will all be considered secondary outcomes. According to the attending physicians’ definition, a hospital stay is the period of time between admission and discharge.

### Participant timeline

On the day before surgery, candidates will be scrutinized according to the inclusion and exclusion criteria. According to their mFI scores, researchers will classify the participants into the frailty group or the nonfrailty group after receiving written informed consent. We’ll keep track of every intraoperative variable.

From the first to the third postoperative day, the patients will be checked on once in the morning and once in the afternoon, and the 3D-CAM score will be taken to gauge the frequency and seriousness of delirium. On the 30^th^ postoperative day, a phone follow-up will be finished, and any issues that develop within 30 days of the procedure will be noted.

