**Methods:**

This study is a prospective, observational, cohort study conducted at a single center with Chinese geriatric patients. Patients who undergo noncardiac surgery and are older than 70 years will be included. A total of 536 noncardiac surgery patients will be recruited from the First Affiliated Hospital of Shandong First Medical University for this study. The Barthel Index (BI) rating will be used to assess the patient’s ability to carry out everyday activities on the 1st preoperative day. The modified frailty index (mFI) will be used to assess frailty. Patients in the nonfrailty group will have an mFI < 0.21, and patients in the frailty group will have an mFI ≥ 0.21. The primary outcome is the incidence of POD. Three-Minute Diagnostic Interview for CAM-defined Delirium (3D-CAM) will be conducted twice daily during the 1st-7th postoperative days, or just before discharge. The secondary outcomes will include one-year mortality, in-hospital cardiopulmonary events, infections, acute renal injury, and cerebrovascular events.

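### The primary outcome, postoperative delirium, is given two incompatible assessment windows (days 1–7 and days 1–3), and neither the outcome definition nor the planning rates say which applies

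*Protocol article*

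**What the plan says.** Three places in the protocol article describe how POD is ascertained.

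- **Abstract, Methods:** the 3D-CAM "will be conducted twice daily during the 1st-7th postoperative days, or just before discharge".
- **Study implementation, Diagnosis of POD:** "The 3D-CAM will be used to evaluate POD twice a day", in a morning slot (8:00–10:00) and an evening slot (18:00–20:00), on postoperative days 1 to 7.
- **Participant timeline:** "From the first to the third postoperative day, the patients will be checked on once in the morning and once in the afternoon", and at these checks "the 3D-CAM score will be taken to gauge the frequency and seriousness of delirium". The next contact listed is the telephone call on day 30.

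The **Primary outcome** section reads in full: "The primary outcome will be the incidence of POD". It gives no time frame.

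The **Sample size calculation** assumes that "the incidence of POD in the frailty and nonfrailty groups was 35.7% and21.7" per cent respectively. The source is described only by "Based on literature review and early study results", again without a time frame.

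**The concern.** A cumulative incidence has a meaning only together with the period over which cases are counted. Here the same instrument, used twice daily for the same purpose, has two different last days, and the section that defines the outcome does not choose between them.

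Two things are at stake. First, staff who work from the Participant timeline would make no assessments on days 4–7, and no later analysis could recover those cases. Second, the sample size rests on two POD rates whose window is unstated. If that window differs from the one used in the study, the planned power of 80% does not apply to the outcome measured.

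This is not a detail that an article may leave to a fuller document. The text gives two conflicting values for part of the primary endpoint.

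**Working it through.** **1. The sections side by side**

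| Section | Instrument | Frequency | Days |
|---|---|---|---|
| Abstract, Methods | 3D-CAM | twice daily | 1–7, or just before discharge |
| Study implementation | 3D-CAM | twice daily (8:00–10:00, 18:00–20:00) | 1–7 |
| Participant timeline | 3D-CAM | morning and afternoon | 1–3 |
| Primary outcome | not stated | not stated | not stated |
| Sample size calculation (rates) | not stated | not stated | not stated |

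The Participant timeline cannot be read as a separate clinical check, because it names the 3D-CAM and delirium.

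**2. Reproducing the plan's sample size**

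Inputs, all from the Sample size calculation: p1 = 0.357 (frailty), p2 = 0.217 (nonfrailty), ratio 0.303, so k = 1/0.303 = 3.300; two-sided α = 0.05, power 0.80, dropout 10%.

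With d = p1 − p2 = 0.140 and p̄ = (p1 + k·p2)/(1 + k) = 0.2496:

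- Uncorrected: n = [1.960·√((1 + 1/k)·p̄(1 − p̄)) + 0.842·√(p1(1 − p1) + p2(1 − p2)/k)]² / d² = 102.1, so 103 frail and 340 nonfrail. This does not match the plan.
- Continuity-corrected: n_c = (n/4)·[1 + √(1 + 2(k + 1)/(n·k·d))]² = 111.2, so 112 frail; 112/0.303 = 369.6, so 370 nonfrail. This matches.
- Dropout: (112 + 370)/0.9 = 482/0.9 = 535.6, so 536. This matches.

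The article does not name the test. The continuity-corrected formula gives its figures exactly, so the power calculations below use it.

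**3. Power at 112/370**

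z = (|p1 − p2| − c − 1.960·s0)/s1, where c = ½(1/112 + 1/370) = 0.00582, s0 is the pooled standard error and s1 the unpooled one; power = Φ(z).

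At the planned rates: (0.140 − 0.00582 − 1.960 × 0.04667)/0.05009 = 0.853, power 80.3%.

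**4. If the planning rates are 7-day rates and assessment stops at day 3**

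Assumption: a share s of first episodes arises on days 4–7, equally in both groups, so each rate is multiplied by (1 − s). The documents give no value for s.

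| s | Rates by day 3 | Power at 112/370 | Total needed for 80%, after dropout |
|---|---|---|---|
| 0% | 35.7% / 21.7% | 80.3% | 536 |
| 5% | 33.9% / 20.6% | 77.5% | 575 |
| 10% | 32.1% / 19.5% | 74.4% | 613 |
| 20% | 28.6% / 17.4% | 67.8% | 713 |
| 30% | 25.0% / 15.2% | 60.5% | 842 |

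**5. If the planning rates are 3-day rates and assessment runs to day 7**

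Under the same assumption each rate is divided by (1 − s).

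| s | Rates by day 7 | Power at 112/370 |
|---|---|---|
| 5% | 37.6% / 22.8% | 83.1% |
| 10% | 39.7% / 24.1% | 85.9% |
| 30% | 51.0% / 31.0% | 96.0% |

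The direction of the effect on power therefore depends on a fact that the article does not state.

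**The case against.** The best defence is that days 1–7 is the evident intention. Two of the three descriptions agree on it, one of them is the dedicated paragraph on diagnosing POD with clock times, and the schedule figure (Fig 1), which is not shown here, may agree as well. The study runs at one centre with trained and examined staff and standardised collection files, so a mixture of schedules is not established. The Background also says that POD typically arises 24 to 72 hours after surgery, which suggests that few cases would be lost after day 3. The difference between an evening slot and an afternoon check may be no more than loose wording.

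Most of this stands, and it limits the size of the problem. It does not remove the contradiction: whatever the figure shows, the text sections disagree, and the article itself considers assessments to day 7 worth scheduling.

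Some stronger readings are tempting, but the documents do not support them.

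- *The planning rates depend on which section staff follow.* They do not. They are fixed inputs from literature and early results; what depends on the window is whether they apply to the outcome measured.
- *Power is certainly lost.* That holds only if the rates are 7-day rates and assessment stops at day 3.
- *A window ending at discharge inflates the odds ratio, because frail patients stay longer.* This is possible in principle, but no length of stay by group is given, so any figure would come from the assumed discharge pattern.
- *Nearly all patients are still inpatients through day 3.* This is not established either. Table 1 excludes hospital stays under 3 days, but the Secondary outcomes section counts stay from admission and recruitment takes place the day before surgery. Discharge before postoperative day 3 is therefore possible.

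**Conclusion.** The point holds as an internal contradiction in the primary endpoint. The same assessment ends on day 7 in two sections and on day 3 in a third, and the outcome definition does not decide between them. It needs to be corrected, because the endpoint is not uniquely defined as the article stands.

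The calculation of 112, 370 and 536 is correct for its inputs. What is open is the window to which 35.7% and 21.7% refer. If they are 7-day rates and 5–30% of first episodes come on days 4–7, equally in both groups, a 3-day window gives power of about 77% down to 60% instead of 80%. The Background's statement on onset points to the upper end of that power range. If they are 3-day rates, a 7-day window gives more than 80%. The late share is assumed throughout. No claim about bias in the odds ratio is made.

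**What to change.** - Bring the abstract, Study implementation, Primary outcome and Participant timeline to one window, and Fig 1 too if it differs. Days 1–7 or until discharge is the natural candidate, since it adds no visits beyond those in the abstract and Study implementation; relative to the Participant timeline it does add assessments on days 4–7. Align the time of the second daily check as well.
- Write that window into the Primary outcome section, and state in the Sample size calculation which window the 35.7% and 21.7% refer to. If the two differ, restate the power.
- Record the date of the first positive 3D-CAM and the number of assessments made for each patient.
- Add a sensitivity analysis restricted to days 1–3, from the same data, to show how far the result depends on the window.
- The Trial status section has recruitment or data collection ending in December 2023, and the article appeared in March 2024, so assessments may already be complete. In that case, report which schedule was actually followed. If assessments stopped at day 3, define and report the outcome as 3-day POD.

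Before data collection the cost is wording, two recorded items and one extra analysis. Afterwards it is a disclosure and an outcome label that matches the data; days 4–7 cannot be recovered if they were not assessed.

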### Recruitment

In the day before surgery, we will recruit the patients and explain the study protocol to them. Before deciding whether to participate, the patient will receive enough time to read and assess the information and ask questions. If the patient refuses to participate, the quality of the perioperative management will not be adversely affected.

### Data collection methods

Researchers who are responsible for data management will collect participant data. The data collection files will be standardized to ensure that all data are recorded and can be analyzed in the future. It will be necessary to have at least two researchers (an operator and a research assistant) collect data in each case, and the research assistant will be responsible for supplementing and improving the Case Report Form (CRF) form.

### Data management

According to the findings of the initial observation, researchers will promptly, completely, and accurately enter data on the CRF. According to the plan, the research coordinator will ensure that the study is conducted. The CRF will be delivered to the researchers in charge of data management after being completed and approved by the project’s general director. One researcher will enter the data, and a second researcher will review it. CRF will be kept in order. The data management is always subject to review by the ethical committee.

### Patient and public participation

In the creation of research questions, study design, intervention designs, outcome measurements, recruiting, or study execution, patients are not directly involved. The patients will be notified by phone or message of any conference presentations and publications at the conclusion of this study.

### Statistical methods

Continuous variables will be subjected to normality tests (such as age). If the data have a normal distribution, the mean ± standard deviation will be used to represent the data. Intergroup comparisons will be made using independent-sample t tests. In the absence of a normal distribution, medians (interquartile range) will be used to express the data, and the Wilcoxon rank sum test will be applied to compare the groups. A categorical variable, such as the sex or complications, will be expressed as a frequency (percentage). We will use either the chi-square test or Fisher’s exact probability approach for intergroup comparisons.

The primary outcomes of POD will be analyzed using a logistic regression model. The correlation between weakness and POD will be calculated using odds ratios (ORs) and 95% confidence intervals (CIs).

Kaplan-Meier survival curves will be used to describe the incidence of secondary outcomes. We will use the log-rank test to compare the differences between groups. A Cox regression model will be used to analyze the influencing factors for 30-day readmissions and complications.

In order to compare the abscission rate between the two groups, the chi-square test will be used.

All statistical analyses will be conducted using the two-sided test with a p value < 0.05 considered statistically significant.

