# Correlation of preoperative frailty with postoperative delirium and one-year mortality in Chinese geriatric patients undergoing noncardiac surgery: Study protocol for a prospective observational cohort study

**DOI:** 10.1371/journal.pone.0295500

**Published:** 2024-03-06

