**Discussion:**

This study will clarify the correlation of preoperative frailty with POD and one-year all-cause mortality in Chinese geriatric patients undergoing noncardiac surgery. Can preoperative frailty predict POD or one-year mortality? In the face of China’s serious aging social problems, this result may have important clinical value for the surgical treatment of geriatric patients.

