According to the inclusion and exclusion criteria, patients will undergo a rigorous screening process. Researchers who have been trained and evaluated will do the preoperative and postoperative follow-up and data collecting for the chosen patients. This research is based on observation. The conclusions will reflect the significance of preoperative frailty assessment and further demonstrate which frailty index indicators are independent risk factors related to POD from the findings of multivariate regression analysis. In geriatric patients undergoing noncardiac surgery, this will serve as a basis for preventing POD.

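### The Cox model is assigned to 30-day readmissions and complications, leaving one-year mortality with Kaplan-Meier curves and an unadjusted log-rank test

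*Protocol article*

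**What the plan says.** The title pairs two outcomes: "Correlation of preoperative frailty with postoperative delirium and one-year mortality in Chinese geriatric patients undergoing noncardiac surgery". The Discussion paragraph of the Abstract repeats the pairing as the aim ("This study will clarify the correlation of preoperative frailty with POD and one-year all-cause mortality in Chinese geriatric patients undergoing noncardiac surgery") and asks "Can preoperative frailty predict POD or one-year mortality". Secondary outcomes lists mortality beside other endpoints: "The incidence of 30-day readmission, one-year all-cause mortality, postoperative complications".

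Statistical methods treats the outcomes in three steps:

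- Delirium gets a logistic model, with odds ratios and 95% confidence intervals.
- Secondary outcomes get a description and a group comparison: "Kaplan-Meier survival curves will be used to describe the incidence of secondary outcomes", then "We will use the log-rank test to compare the differences between groups". No strata or covariates are named.
- One regression model is named for secondary outcomes, and its scope is stated: "A Cox regression model will be used to analyze the influencing factors for 30-day readmissions and complications".

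The only mention of multivariable regression is in the main Discussion and concerns delirium: "which frailty index indicators are independent risk factors related to POD from the findings of multivariate regression analysis".

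**The concern.** The article names a survival regression model and gives it to other secondary outcomes, not to the one in the title. An analyst following this text would report two mortality curves and a p value.

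Two things would then be missing. One is a relative measure of the frailty-mortality association, such as the odds ratio planned for delirium. The other is any allowance for age. The study is not randomised (Methods/Design), entry is at 70 years or more with no upper limit (Participants), and the Discussion describes frailty as related to ageing. If frail patients are older and older patients die more often, a crude comparison mixes the two effects. The answer to the article's own question about predicting one-year mortality would be hard to interpret.

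**Working it through.** **The plan's own figure.** The only numerical design statement is the sample size for delirium. Inputs from Sample size calculation: 35.7% against 21.7%, frail to nonfrail ratio 0.303, two-sided α 0.05, power 0.80. The two-proportion formula gives 103 frail and 340 nonfrail without continuity correction. With the correction it gives 112 frail and 112/0.303 = 369.6, so 370 nonfrail, exactly as stated. Then 112 + 370 = 482, and 482/0.9 = 535.6, so 536. The calculation is sound, but it concerns delirium only. The article gives no mortality rate, hazard ratio, number of deaths or power for mortality.

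**Text check, by outcome.**

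| Outcome | Description and test | Regression named |
|---|---|---|
| Delirium | chi-square or Fisher | logistic, OR with 95% CI |
| 30-day readmission, complications | Kaplan-Meier, log-rank | Cox |
| One-year mortality | Kaplan-Meier, log-rank | none |

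**Illustration of size.** None of the following inputs is in the document except the group sizes.

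- True frailty hazard ratio at a given age: 1.
- Age standard deviation: 5 years in both groups.
- Frail patients older by d = 0 to 3 years.
- Hazard ratio per year of age, h: 1.05 or 1.10.
- One-year mortality of 5% or 10% at the mean age of the nonfrail group.
- 112 frail and 370 nonfrail patients, all followed for one year.

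The spurious crude hazard ratio is approximately h^d. The smallest is 1.05^1 = 1.05 and the largest 1.10^3 = 1.33.

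Share of 3,000 simulated studies per setting in which the two-sided 5% log-rank test rejects:

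| Mortality | h | d = 0 | d = 1 | d = 2 | d = 3 |
|---|---|---|---|---|---|
| 5% | 1.05 | 5.3% | 4.9% | 6.7% | 7.9% |
| 5% | 1.10 | 5.2% | 5.7% | 9.0% | 11.9% |
| 10% | 1.05 | 5.1% | 5.7% | 6.4% | 8.7% |
| 10% | 1.10 | 5.1% | 7.0% | 9.9% | 17.3% |

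With no age gap the test holds its level. With a gap of 1-3 years, rejection runs from about 5% to 17%. The simulation error near 5% is √(0.05 × 0.95/3000) = 0.4 percentage points.

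**Deaths available for a model.** At an assumed overall mortality of 5-10%, 482 × 0.05 = 24 and 482 × 0.10 = 48 deaths. Two covariates have 24/2 = 12 to 48/2 = 24 deaths each. Four would have 24/4 = 6 to 48/4 = 12, and fewer if operation type has several levels.

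**The case against.** **It may be silence.** This is a journal article, and covariate lists are normally left to a fuller plan. None is given here for any model, including the delirium model. That stands: missing covariates are not the point, and a reader who infers that no adjusted mortality analysis exists anywhere goes further than the article, which does not say that the log-rank test is the only one. What remains is that the scope of the Cox model is written down and mortality is outside it.

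**A correlation needs no adjustment.** For mortality the article promises a correlation and asks about prediction. Where it states its own aim in terms of independent risk factors, it refers to delirium. A crude comparison can show whether frail patients die more often, and the curves would give absolute mortality by group. This is fair, and it limits what is at stake. It does not supply a relative effect measure, and it leaves the reader unable to tell frailty from age.

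**The consequence can be overstated.** A reader might infer that the log-rank test would credit an age effect to frailty. The document gives no age gap or mortality gradient, age is not an item of the frailty index, and under the assumptions above most simulated studies do not reject. Nor is mortality the only outcome with a time to event, since 30-day readmission has one too.

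**The data may not be in place.** Participant timeline describes telephone follow-up only at day 30. Trial status mentions one-year mortality measurements, but no section describes a one-year contact or the recording of death dates. Recruitment (Participants) and completion including one-year mortality (Trial status) both end in December 2023, so later recruits could lack a full year. A sentence about Cox regression does not settle that.

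**Conclusion.** The point holds as a misassigned model. As written, one-year mortality gets no hazard ratio and no adjustment, while the Cox model goes to outcomes that are not in the title. The primary outcome and the sample size are unaffected.

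The textual finding needs no assumption. Its numerical size does: a spurious crude hazard ratio of about 1.05-1.33 and a log-rank false-positive rate of about 5-17% hold only for the assumed 1-3 year age gap, hazard ratio of 1.05-1.10 per year, age spread and mortality. Small gaps do almost no harm to the test, and larger ones do moderate harm. The document does not show which applies.

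**What to change.** Extend the Cox sentence in Statistical methods along these lines: *One-year all-cause mortality will be analysed by Cox regression, with time from surgery to death, censored at 365 days or last contact. Frailty group and age (continuous) are the prespecified covariates, and the adjusted hazard ratio for frailty will be reported with its 95% confidence interval. Kaplan-Meier curves and the log-rank test are descriptive. Models that add sex and operation type are sensitivity analyses.*

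Fixing two covariates in advance suits the possibly small number of deaths and avoids choosing the model after they have been counted. Adjusting for age alone will not remove all confounding, which is the reason for the sensitivity models.

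The cost is a slightly wider interval and a little more analysis. Date of death or last contact must be recorded up to one year, and the follow-up description should say so, because it currently stops at day 30. The sample size does not change.
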